### Study Endpoints

#### Primary Endpoint

The primary outcome was post-AMI infection during hospital admission, which was defined as infection requiring antibiotics (reflecting the clinical influence of infection compatible with the necessity for additional treatment) (18). The types of infections included pulmonary infections, urinary infections or others (including abdominal sepsis, primary bacteremia, and unidentified primary infection site) based on the clinical records during hospitalization. Appropriate antibiotics were used once infection was confirmed (19). The antibiotics were validated by the hospital infection control committee that approved the initiation of therapy for each infection case.

#### Secondary Endpoints

The secondary endpoints were in-hospital all-cause mortality and major adverse cardiovascular events (MACE) including all-cause death, recurrent myocardial infarction, target vessel revascularization, and stroke (20) (Table 2). All these adverse events will be recorded in detail during in-hospital period.

**Table 2 T2:** Outcome definitions in MACE.

**Term**	**Definitions**
All-cause death	Any death recorded between the date of enrollment and the end of data linkage.
Recurrent myocardial infarction	Characteristics of MI occur after 28 days following an incident MI^15^.
Target vessel revascularization	Any revascularization procedure involving PCI of the target lesion or surgical bypass of the target vessel.
Stroke	The presence of a new focal neurological deficit thought to be vascular in origin, with signs or symptoms lasting > 24 h.

*MACE, major adverse cardiovascular events; MI, myocardial infarction; PCI, percutaneous coronary intervention*.

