Given these data, this research protocol aims to develop and validate a practical risk score to identify the risk of post-AMI infection in patients with STEMI undergoing PCI. And this new risk score based on seven simple independent predictors would be divided into four levels according to the corresponding marks (low-, moderate-, high-, and very high-risk groups) to improve the clinical utility. Therefore, the present risk score could be easily applicable in clinical practice for identifying patients at high-risk of infection and in-hospital outcomes in patients with STEMI undergoing PCI and may help clinical decision-making allowing for timely measures to improve clinical outcomes.

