### Study Population

STEMI was defined as the manifestation of typical chest pain and concomitant symptoms for ≥ 30 min but <12 h, with ST-segment elevation ≥ 1 mm in ≥ 2 continuous leads or new or undetermined duration of left branch bundle block accompanying with ≥ 2 times increase in troponin I or T (15).

The inclusion criteria were as follows: (a) age ≥ 18 years; patients with STEMI undergoing PCI, admitted to the cardiac intensive care unit; (b) patients could understand and agree with informed consent.

The exclusion criteria were as follows: (a) patients diagnosed with infection or treated with antibiotics prior to admission; (b) patients with tumor or chronic inflammatory diseases; (c) patients on hemodialysis at admission; (d) patients undergoing emergency cardiac surgery; (e) patients died within 24 h after admission; (f) readmission to hospital; and (g) patients with missing variables that are needed to calculate the risk scores.

Eligible patients were consecutively enrolled between January 1st 2010 and May 31st 2016, which were served as a development cohort. In accordance with the inclusion and exclusion criteria, patients enrolled from June 1st 2016 to May 31st 2018, with complete data regarding risk factors identified in the development cohort, will be served as a validation cohort. Furthermore, the patients screened according to the criteria in other centers will be enrolled for external validation.

To extend the application, this risk score will also be validated in our previous study including patients diagnosed with non-ST-elevation acute coronary syndrome (NSTE-ACS) following PCI according to the same exclusion criteria (16). This retrospective cohort study was designed to evaluate the association between parenteral anticoagulation therapy and clinical outcomes in patients mentioned above. Patients with principal discharge diagnosis of non-ST elevation myocardial infarction (NSTEMI) or unstable angina (UA) and underwent PCI during the index hospital stay were included. And patients with elevated cardiac biomarker and without new ST-elevation on ECG prior to index PCI were classified as NSTEMI while those were classified as UA if there were no positive cardiac biomarker findings and without new ST-elevation on ECG prior to index PCI (16).

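### The MACE definitions in Table 2 do not fit the in-hospital recording window: recurrent MI counts only after 28 days, and death runs to the end of data linkage

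*Protocol article*

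**What the plan says.** The Secondary Endpoints section of the protocol article states: "The secondary endpoints were in-hospital all-cause mortality and major adverse cardiovascular events (MACE) including all-cause death, recurrent myocardial infarction, target vessel revascularization, and stroke". On the observation window it adds: "All these adverse events will be recorded in detail during in-hospital period". The Introduction describes the intended use of the score in the same terms: "identifying patients at high-risk of infection and in-hospital outcomes in patients with STEMI undergoing PCI".

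Table 2, in the same section, then defines the MACE components. Three rows matter here:

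- Recurrent MI: "Characteristics of MI occur after 28 days following an incident MI".
- All-cause death: "Any death recorded between the date of enrollment and the end of data linkage".
- Target vessel revascularization: "Any revascularization procedure involving PCI of the target lesion or surgical bypass of the target vessel".

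Under Study Population, the index STEMI requires "typical chest pain and concomitant symptoms for ≥ 30 min but <12 h", and readmission is an exclusion. The article describes no contact or data source after discharge.

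**The concern.** The text and the table set different clocks for one composite endpoint. The text stops recording at discharge. The recurrent-MI row does not start counting until 28 days have passed. The death row ends at a data-linkage date that is mentioned nowhere else and need not coincide with discharge.

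Taken literally, the MI rule discards the re-infarctions that an in-hospital endpoint is meant to capture. The death row could bring in deaths that the in-hospital endpoint should leave out. Under Data Collection and Missing Data, two investigators collect outcomes independently and a third resolves differences. With these definitions, one could follow the text and the other the table, and both would be following the protocol. The external centers would meet the same ambiguity. The resulting MACE rate would be hard to interpret and would not be comparable with an ordinary in-hospital MACE rate.

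**Working it through.** **The plan's own figure.** Under Sample Size Consideration, 10 events per variable × 8 variables = 80 infections, and 80 / 0.10 = 800 patients. This reproduces exactly. It rests on infections alone, so the MACE definitions do not enter it.

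**The windows side by side.** Let T be the time from the index MI to a re-infarction and L the time from the index MI to discharge. The recurrent-MI row requires T > 28 days. The recording sentence requires T < L. An event counts only if 28 < T < L, which is impossible unless L > 28 days. Symptoms at presentation have lasted under 12 hours, so the 28-day clock starts at most about half a day before presentation, and L is close to the length of stay. This step needs no outside figure.

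**How many patients can qualify.** Length of stay is not in the documents. Assume it is log-normal with median m and log-SD s. Then P(L > 28) = 1 − Φ(ln(28/m)/s):

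- m = 7, s = 0.5: 1 − Φ(1.386/0.5) = 0.3%
- m = 7, s = 0.6: 1 − Φ(1.386/0.6) = 1.0%
- m = 10, s = 0.6: 1 − Φ(1.030/0.6) = 4.3%

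**How many events can qualify.** This is a wider sensitivity check. It takes s from 0.4 to 0.8 and adds two further assumptions: a constant re-infarction hazard during the stay, and 8 to 24 in-hospital re-infarctions per 800 patients (1% to 3%). The countable share is then E[max(L − 28, 0)] / E[L], obtained by simulation.

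| Assumed median stay | Patients beyond day 28 | Share of inpatient days countable | Expected countable events out of 8 to 24 |
|---|---|---|---|
| 5 to 7 days | 0.001% to 4.2% | 0.001% to 5.5% | about 0 to 1.3 |
| 10 days | 0.5% to 9.9% | 0.2% to 11% | 0.02 to 2.7 |
| 14 days | 4.2% to 19% | 1.4% to 19% | 0.1 to 4.6 |

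Even in the most favourable cell (median 14 days, log-SD 0.8), about 81% of in-hospital re-infarctions are excluded (1 − 0.193). If the hazard is higher early in the stay than later, the loss is larger.

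**The other rows.** The death row has no discharge limit, so it does not match the in-hospital window either. The revascularization row names the vessel but, for PCI, counts only the lesion. Repeat PCI elsewhere in the same vessel is left out, while bypass of the vessel is counted.

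**The case against.** The strongest reply is that Table 2 may be correct and the text too narrow. In the endpoint sentence, the in-hospital qualifier stands directly before mortality only, and two rows of the table suggest a longer horizon. This stands in part: the documents do not show which side is the error. It does not remove the conflict, because the recording sentence covers all the listed events and no later follow-up is described.

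A second reply is that the incident MI could mean an infarction before the index one. In patients with a previous MI, the index STEMI would then itself count as the recurrent event, so this reading does not rescue the row.

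Three stronger conclusions might be inferred, and the documents do not support them:

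- *That two of four components fail and MACE collapses to death and stroke.* PCI of the target lesion and bypass of the target vessel still count. The revascularization row is a mismatch of name and definition.
- *That the score or its validation is undermined.* The primary endpoint is infection, and the Data Analysis section names no MACE analysis. In-hospital mortality is also a secondary endpoint in its own right.
- *That the share of countable events is known.* It depends on an assumed length of stay, and with long, widely spread stays a handful of events would remain.

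**Conclusion.** The contradiction is real and follows from the text alone: in-hospital recording and a 28-day minimum cannot both define recurrent MI sensibly, and the death row does not fit that window either. The consequence is an under-count of re-infarction within a secondary composite. It reaches the MACE total through patients whose only event is an in-hospital re-infarction by day 28.

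The size is conditional. About 0.3% to 4% of patients could contribute if the median stay is 7 to 10 days with a log-SD of 0.5 to 0.6, and up to 19% in the longest-stay scenario examined. The primary endpoint and the sample size are untouched. The point should be corrected, but it does not threaten the study's main result. The revascularization wording is minor.

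**What to change.** State one observation window and apply it to every row of Table 2. For the in-hospital endpoint that the text describes:

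- define recurrent MI as a new infarction, distinct from the index event, occurring before discharge from the index admission, with no 28-day minimum, and state how it is told apart from the evolving index infarction;
- define all-cause death as death before that same discharge;
- make the name and content of the revascularization row agree, either by counting PCI of any segment of the target vessel or by renaming the row.

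If a longer horizon was intended, the alternative is to state a follow-up period beyond 28 days, with its data source, for all components. The article describes none, so this would be the larger change.

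The wording change is a few lines in one table. The real cost depends on what has already been done. Enrollment ran to May 31st 2018 and outcome collection is described in the past tense. If abstraction followed the 28-day rule, the MACE records must be re-checked for re-infarctions that were passed over. If deaths were taken from linkage, those after discharge must be separated out.

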### Statistical Analysis

#### Sample Size Consideration

A rule of thumb, namely, that the event per variable (EPV) was 10 or greater under this circumstance was applied for the sample size determination. Given no more than 8 risk factors in developing a predictive model, thus at least 80 infections were needed. According to the previous studies (3), the incidence of infection was 10%, and at least 800 patients should be finally included.

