### Data Collection and Missing Data

Clinical data including patient demographics, diagnosis, medical histories, clinical and laboratory characteristics, medication treatment, procedural details and main outcomes were obtained through review of electronic medical records. The principal data, such as clinical outcomes, were collected by two investigators independently, and inconsistent data were verified by a third investigator.

Variables were included as candidates for this risk score after removing variables with ≥ 10% missing values (Table 1), and for those with incomplete data, we assumed that patients with the missing data ≤ 5% occurred at random depending on the clinical variables and used multiple imputations. This risk score model was developed based on imputed complete cases.

**Table 1 T1:** Observations and endpoints.

**Category**	**Method and materials**	**Observation and examination items**
Demographic characteristics	Interview	Age, sex and smoking status.
STEMI	Medical examination and interview	Onset of STEMI, date of hospitalization, description of treatment.
History of present illness/previous history/therapies	Interview	Previous history of cardiovascular and cardiovascular risk-related diseases and history of treatment (Hypertension, MI, CABG, COPD, AF, stroke, PCI, sudden cardiac arrest, thrombolysis, pericardial effusion, PCI lesion).
Physical findings	Medical examination	SBP, DBP, heart rate and Killip class.
Family history	Interview	Coronary artery diseases, hypercholesterolaemia and ischaemic cerebral infarction in relatives to the second degree of kinship.
Hematological and biochemical examinations	Serum and urine	The following parameters will be measured from blood acquired within 24 h after admission: WBC, eGFR, creatinine, albumin, hemoglobin, TG, TC, total bilirubin, direct bilirubin, LDL, HDL, ALT, CO_2_ combining power, Urine PH.
Heart function	Echocardiography	LVEF, LVDd, LVDs.
Medication during hospital stay	Electronic medical record	Statins, Warfarin, Tirofiban, ARB, CCB, ACEI, β-blockers, insulin, metformin, PPI, diuretics and nitrates.
Procedural characteristics	Electronic medical record	PCI approach, multi-lesion, contrast volume, number of stents and total length of stents.

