#### Data Analysis

The student's *t*-test or Wilcoxon rank-sum test was used to compare the continuous variables and the chi-square test or Fisher exact test was used as appropriate for categorical variables for the comparison of patients with or without infections in both datasets.

The risk score was developed using a backward stepwise logistic regression model. All candidate predictors were included in the development of the risk score, and to avoid overfitting data and select the best subset of risk factors, a bootstrap method was used. For missing data, 10 multiple imputations were performed using the SAS MI procedure, and 100 bootstrap repeats were conducted for each imputation. Variables selected in at least 90% of 1,000 bootstrap repeats were included in the final model. The risk score was developed for each imputed data via using the selected variables and the SAS MIANALYZE procedure was used to combine the results of the analyses. For this risk score, the scoring method was analogous to that of Sullivan et al. (21) and was used based on the developed risk score. For the scoring purpose, continuous variables were categorized into groups regarding the clinical significance. The risk score of post-AMI consisted of four levels (low-risk, moderate-risk, high-risk, and very high-risk) in order to enhance the clinical utility.

Both discriminatory accuracies assessed by the C-statistic and calibration measured by the Hosmer-Lemeshow χ^2^ statistic and calibration plot were used to evaluate the predictive accuracy of the risk score. The bootstrap method with 1,000 bootstrapped replications was used to perform an internal cross-validation of the risk score. The average of the C-statistic was reported. In addition, external validation and subgroup validation (older, gender, diabetes, anemia, and chronic kidney disease) of the risk score model was conducted to assess the stability of the model. The risk score was also validated in patients with NSTE-ACS undergoing PCI, and the area under curve (AUC) of this risk score was compared to the previous scoring systems (6, 7). Furthermore, comparison of the area under the receiver operating characteristic (ROC) curve was according to the nonparametric approach of DeLong et al. (22). To evaluate the clinical utility of this risk score, decision curve analysis was introduced and the risk score with a higher net benefit indicated a better clinical effect (23).

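### The events-per-variable calculation divides by 8 risk factors, but the planned selection screens up to about 55 candidates, so 80 infections do not give 10 events per variable for this analysis

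*Protocol article*

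**What the plan says.** Under Sample Size Consideration, the protocol article adopts a rule of thumb: "the event per variable (EPV) was 10 or greater under this circumstance was applied for the sample size determination". It then fixes the denominator and the events: "Given no more than 8 risk factors in developing a predictive model, thus at least 80 infections were needed". The patient number follows from an incidence taken from earlier work: "the incidence of infection was 10%, and at least 800 patients should be finally included".

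The Data Analysis section describes how predictors are chosen. The method is backward stepwise logistic regression, and "All candidate predictors were included in the development of the risk score". The final model is set by a bootstrap rule: "Variables selected in at least 90% of 1,000 bootstrap repeats were included in the final model".

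Data Collection and Missing Data says where the candidates come from: "Variables were included as candidates for this risk score after removing variables with ≥ 10% missing values (Table 1").

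The Introduction says that the finished score rests on seven predictors.

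**The concern.** When predictors are chosen by looking at the data, overfitting depends on how many parameters were examined, not on how many survive. If only survivors counted, any amount of screening would appear to satisfy an EPV rule, provided the final model was small. The denominator of 8 sits next to a seven-predictor score, while the analysis section screens the whole candidate list. If 8 was instead meant as the number of candidates, it conflicts with the two sections that draw candidates from Table 1 and enter all of them. On either reading the sample-size paragraph does not describe the planned analysis.

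At stake are the points themselves. With few events per candidate, the selected set tends to be unstable and the retained coefficients tend to be too large. The coefficients are turned into points and then into four risk levels intended for clinical use, so any exaggeration carries through.

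**Working it through.** **Inputs from the Protocol article**
- Target EPV 10, denominator 8, incidence 10% (Sample Size Consideration).
- Candidates: Table 1 variables less those with 10% or more missing (Data Collection and Missing Data). All of them enter selection (Data Analysis).
- Seven predictors in the finished score (Introduction).

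**Step 1: reproduce the plan's figures**
- Infections = EPV × variables = 10 × 8 = 80.
- Patients = infections / incidence = 80 / 0.10 = 800.

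Both match. The multiplication is right; the issue is what the 8 counts.

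**Step 2: count the candidates in Table 1**

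Demographic 3, history 11, physical findings 4, family history 3, laboratory 14, echocardiography 3, in-hospital medication 12, procedural 5.

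3 + 11 + 4 + 3 + 14 + 3 + 12 + 5 = 55.

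This leaves out the row on STEMI onset, hospitalization date and treatment (adding its three items gives 58) and counts Killip class once.

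**Step 3: EPV on candidates at the stated minimum, 80 / P**

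| Candidates P | Basis | EPV at 80 infections | Infections for EPV 10 |
|---|---|---|---|
| 58 | STEMI row included | 1.38 | 580 |
| 55 | tally above | 1.45 | 550 |
| 43 | without medication (55 − 12) | 1.86 | 430 |
| 38 | without medication or procedural (43 − 5) | 2.11 | 380 |
| 30 | assumed | 2.67 | 300 |
| 20 | assumed | 4.0 | 200 |
| 8 | the plan's denominator | 10.0 | 80 |

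For 55 candidates, 550 / 0.10 = 5,500 patients. This shows the size of the gap and is not a request. Coding Killip class or other categories as dummies would raise P and lower EPV further.

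**Step 4: what the denominator implies for shrinkage (illustration only)**

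The expected uniform shrinkage S solves n = P / ((S − 1) ln(1 − R²/S)), where R² is the Cox-Snell value. At 10% prevalence the maximum R² is 1 − exp(2(0.1 ln 0.1 + 0.9 ln 0.9)) = 0.478. The article gives no explained variation, so I assume a Nagelkerke R² of 0.15 to 0.30. That makes R² 0.478 × 0.15 = 0.072 to 0.478 × 0.30 = 0.143. At n = 800:
- P = 55: S about 0.53 to 0.70. Check at the lower end: (0.53 − 1) × ln(1 − 0.0717/0.53) = 0.0683, and 55 / 0.0683 = 805.
- P = 8: S about 0.88 to 0.94.

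The first range applies to an unselected 55-parameter fit. It is not an estimate for the model left after the 90% bootstrap rule.

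**The case against.** Several points on the other side have force.

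- **The 80 and 800 are floors.** The development cohort is every consecutive eligible patient from January 2010 to May 2016, and its size is not stated. A reader might infer that the study's EPV is 1.5. The article does not support that: 1.5 is the value at the planned minimum, and the achieved value may be higher. What stands is that the stated adequacy criterion does not deliver what it claims.
- **The 55 is a reader's tally.** Table 1 is titled as a list of observations and endpoints, and it is unclear whether it stands before or after the missing-data filter. It also omits diabetes, a planned subgroup variable, so it is not a clean candidate list. This is why a range is given. Nothing in the article brings the number to 8.
- **Safeguards exist.** Bootstrap selection, bootstrap internal validation, a later cohort, other centres and calibration plots are all planned. They may temper overfitting or expose it. They do not reduce the number of variables screened, so they do not justify a denominator of 8. A reader might go further and predict how few or how many variables the 90% rule would keep. The article states no significance level for staying in the model, so no such prediction can be made from it.
- **Which cohort the 800 describes.** A reader might infer that 800 is the total across both cohorts, leaving development short even on 8 variables. The paragraph ties the 80 infections to developing the model, so the development cohort is the more natural reading. The wording only needs to say so.

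**Conclusion.** The point holds as a mismatch of denominator, not as an arithmetic error. The sample-size paragraph claims an EPV of 10 or more on 8 risk factors, while the analysis screens all candidates that survive the missing-data filter. At 80 infections the EPV on candidates is about 1.5 at the upper tally of 55 and 4.0 if only an assumed 20 remain. Only 8 candidates restore 10.

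The conclusion rests on three things: Table 1 being the source of the candidates, as Data Collection and Missing Data indicates; each variable counting as one parameter, which is generous to the plan; and the events being at the stated minimum. Reading the 8 as the final-model size is an inference from the seven-predictor score and the selection procedure. The alternative reading produces a direct conflict within the article instead. The article does not allow a statement of the EPV achieved or of how inflated the final points will be.

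**What to change.** 1. In Sample Size Consideration, define EPV on candidate parameters (dummy categories counted) in the development cohort. Withdraw the statement that 80 infections give an EPV of 10 for this analysis.
2. Report the actual number of development-cohort infections, the candidate count after the missing-data filter, and the resulting EPV.
3. Do one of the following:
   - limit the candidates on clinical grounds, without looking at the outcome, to a number that the infections support; or
   - estimate a uniform shrinkage factor by bootstrap, repeating the whole selection procedure in each resample, and apply it to the coefficients before they become points.
4. State that the 800 refers to the development cohort.

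The cost is some rewording, slightly more analysis and a less favourable stated EPV. No extra patients are needed. Enrolment was set to end in May 2018, so a shortened list should be presented as chosen blind to outcome, not as originally prespecified.
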